## 1. Specific Aims

1. Develop a multi-pronged, Mediterranean Diet Nutritional Intervention (MDNI) behavior change strategies including: diet/lifestyle education; discounted access to key Mediterranean diet foods; electronic education platforms and reminders. MDNI components will be refined via surveys, literature review and local/national firefighter input including labor/management and fire service focus groups.

Hypothesis (1). Cost-effective, fire-service MDNIs will be developed for the cluster-randomized, career firefighter diet intervention.

2. Cluster Randomized Diet Intervention-Phase I- the Indianapolis Fire Department (IFD) has over 1,000 members. All 44 IFD firehouses will be cluster randomized into two groups and then individual members will be consented regarding study participation. Group 1 will receive an active 12-month MDNI, while Group 2 will receive no intervention. Firefighters categorized as "Administrative Staff" by the IFD will also be approached for participation and if they consent, be assigned to Group 1 because they are not assigned to specific firehouses.

3. Cluster Randomized Diet Intervention -Phase II: Group 1 will cross-over to "self-sustained continuation" for 12 months to examine persistence of behavior change during this less intense, self-directed maintenance diet intervention. Group 2 will cross-over to receive the MDNI for 6 months (assessing a shorter MDNI), followed by a final 6 months of self-sustained continuation. An additional neighboring fire department, Fisher's (IN), will have its 6 firehouses randomized to receive the MDNI (Group 3) or no intervention (Group 4) for six months, and then individual members will be consented regarding study participation. After 6 months, the 3 stations in the MDNI (Group 3) will cross-over to "self-sustained continuation" for the last 6 months to examine persistence of behavior change during this less intense, self-directed maintenance diet intervention. Group 4 will cross-over to receive the MDNI for 6 months (assessing a shorter MDNI).

4. A similar 12-month Cluster Randomized Diet Intervention in the six fire stations of the Fishers (IN) Fire Department with a cross-over by the control group to intervention after 6 months will also be done.

Our existing modified Mediterranean diet score (mMDS) will be further integrated with other validated scores and nutrition questionnaires. Questionnaires, mMDS and clinical data will be collected longitudinally throughout both phases of the Nutritional Intervention. The complete questionnaire has been entered into Qualtrics and is attached for the IRB's review.

Hypotheses (2-3). Both MDNI lengths will improve mMDS, reduce weight, and improve Cardiovascular Disease (CVD) risk profiles in career firefighters. The 12 month MDNI will produce greater persistence of adherence than a 6 month MDNI. Cost-effective methods that combine messaging and discounts for improving firefighters' diets will be developed and validated, and these low cost methods will be adaptable for widespread translation and implementation throughout the career fire service.

5. a. Conduct a nested evaluation of adherence biomarkers (urine tyrosol and hydroxytyrosol and plasma fatty acids) among randomly selected participants in the two Indianapolis MDNI arms (MD intervention vs. control, up to 100 in each).
- 5.b. Blood samples will also be stored for future analyses.
- 5.c. Stool samples will also be stored for microbiome analyses.

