**4.2. Indicate the study's duration - and the estimated date of study completion**

2 years. December 2018

**4.3. Indicate the total number of participants (if applicable, distinguish between the number of participants who are expected to be screened and enrolled, and the number of enrolled participants needed)**

1,000 career firefighters (500 assigned to group 1 and 500 assigned to group 2). We will approach as many eligible members as possible to consent at least 500 and up to 1,000 participants maximum. For the biomarkers nested study, a total of up to 100 firefighters, selected at random evenly from the existing study arms in Indianapolis

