**4.4. List inclusion criteria**

IFD and Fishers members eligible for study consent and participation will include those: a)

permanently assigned to one of the 44 IFD stations or one of the 6 Fishers stations; b) with a fire department-provided medical exam in the last two years; c) at least 18 years of age; and d) full duty, modified or restricted duty status at the time of consent; OR e) Firefighters categorized as “Administrative Staff” by the IFD or Fishers will also be approached for participation and if they consent, be assigned to Group 1 because they are not assigned to specific fire houses.

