### **Follow-up Assessments:**

Every consented participant (regardless of intervention assignment) will be requested to complete the following every 6 months over 4 additional visits after the baseline assessment over the two years of the study:

The comprehensive nutritional-lifestyle questionnaire will be repeated (detailed above), as will the anthropometric measures (height, weight and body fat and resting blood pressure) will be collected in the same manner as described above for the baseline assessment.

Every 12 months, the Fire department provided, annual occupational medicine examinations (part of the firefighters’ usual care unrelated to the present study) will be provided by Public Safety Medical as per existing IFD/ Fishers policies. For consented participants ONLY, the medical exam results will be transferred to the Harvard Chan research team using the same established coded data transfer methods as described above for the baseline assessment of the same data points.

Consented participants will be assigned to Group 1 (Phase 1 nutritional intervention) or Group 2 (No intervention) according to their fire station’s cluster randomization.

For the nested biomarkers study the recruitment of participants will start in phase II following the below timeline:

Figure1. Current parent study timeline and biomarkers proposal timeline (in orange, the proposed study timeline)

[figure not shown]

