and longitudinal data analysis, as needed. Differences in the mean values of a quantitative variable between two groups will be assessed using the independent t-test whereas differences in mean values among three or more groups will be examined using the analysis of variance (ANOVA) technique (or non-parametric Wilcoxon and Kruskal-Wallis tests, respectively, as appropriate). Differences in qualitative characteristics will be compared using the chi-square test, or Fisher's exact test, or McNemar's test (for paired comparisons), as appropriate. Statistical significance for all analyses will be  $p < 0.05$ , and all tests will be two-tailed.

Phase 1: During the first 12 months of the nutritional intervention, **groups 1 (Mediterranean Diet intervention) and 2 (no intervention) will be compared directly on an intention to treat basis according to the randomization of each participant's fire house.** As several outcomes will be assessed on each participant throughout the study (3 annual medical exams and 5 semi-annual assessments (where weight, mMDS, etc. will be evaluated)), repeated measures techniques, such as mixed modeling and generalized estimating equation models, will be utilized to estimate changes over time on key outcomes. We will take into consideration the specific variance-covariance structure of correlated measurements. After adjusting for baseline and time-dependent covariates, changes in the outcomes of interest will be assessed and compared among groups. We expect our greatest power to be for within-group changes (paired comparisons).

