## 6. Recruitment Methods

### 6.1. Does the study involve the recruitment of participants?

☐ No: If no, skip to 7.1

☒ Yes: If yes; indicate how, when, where, and by whom participants will be recruited

**6. How:** Up to 1000 IFD members with permanent station assignments at one of the 44 Indianapolis fire houses will be recruited. The initial approach will be through a written announcement from the Chiefs of the Indianapolis Fire Department (IFD)/ Fishers FD and the firefighters' local union presidents (see attached letter) informing the IFD/ Fishers FD of the inauguration of the study and their opportunity to voluntarily participate. Next, human subjects-trained staff from Public Safety Medical (PSM) will visit each fire house to approach IFD/Fishers members for informed consent and determine their eligibility. Their recruitment script is attached. IFD/ Fishers members eligible for study consent and participation will include those: a) permanently assigned to one of the 44 IFD stations or one of 6 Fishers stations; b) with a fire department medical in the last two years; c) at least 18 years of age; and d) full, modified or restricted duty status at randomization; OR e) Firefighters categorized as "Administrative Staff" by the IFD/ Fishers will also be approached for participation. The fire department will notify PSM regarding criteria a, c, d and e and PSM has a record b (medical exams). First, they will provide a brief overview of the study to the firefighters by reiterating the information from the Chief and Union President's letter and the approved informed consent form. They will inform the fire house of its intervention assignment in the study – in other words, whether they will be receiving the nutritional intervention immediately (In Phase 1); or after 12 months (Phase 2). Next, each member will be offered an informed consent form to review on his/her own and will be allowed at least 15 minutes and longer if desired to review it on their own and to discuss it with their colleagues or others. Finally, each member will have a chance to ask the PSM staff questions individually in private areas of the fire house and may decide to sign the form or decline. IFD/Fishers members will be assured that participation status in the study is completely voluntary and will have no bearing on their employment with the department or on the occupational health care they receive from PSM. Consented participants will be assigned to the Phase 1 nutritional intervention (Group 1) or No intervention (Group 2) according to their fire station's cluster randomization. "Administrative" firefighters who consent will be assigned to Group 1 because they are not assigned to specific fire houses. For the biomarkers study randomly 100 participants (50 in each group) will be invited to participate in the study via email at the same time as the follow-up reminder. The recruitment will stop when we reach 60 participants (30 in each group)

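### Administrative staff are placed in Group 1 by rule, not by randomisation, and nothing takes them out of the Group 1 v Group 2 intention-to-treat comparison

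*Protocol*

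**What the plan says.** Section 1 (Aim 2) sets the unit of randomisation: "All 44 IFD firehouses will be cluster randomized into two groups and then individual members will be consented regarding study participation". The same aim says that consenting IFD administrative staff will "be assigned to Group 1 because they are not assigned to specific firehouses". Section 4.4 admits them under a separate criterion (e) and repeats the rule ("be assigned to Group 1 because they are not assigned to specific fire houses"). Section 6.1 states it a third time: "firefighters who consent will be assigned to Group 1 because they are not assigned to specific fire houses".

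Under Follow-up Assessments in section 4.6, assignment is described in general terms: "Consented participants will be assigned to Group 1 (Phase 1 nutritional intervention) or Group 2 (No intervention) according to their fire" station's randomisation.

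For Phase 1, section 5.1 says that Groups 1 and 2 "will be compared directly on an intention to treat basis according to the randomization of each" participant's fire house. It plans repeated-measures models and adds: "After adjusting for baseline and time-dependent covariates, changes in the outcomes of interest will be assessed and compared among groups".

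Section 4.3 plans 500 per group, with at least 500 participants in total, and draws the biomarker sample "selected at random evenly from the existing study arms in Indianapolis". No section excludes administrative staff from any Group 1 v Group 2 comparison, analyses them separately or gives them a cluster.

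**The concern.** Intention to treat protects a comparison because each person is analysed in the arm to which chance assigned them. Chance assigned the administrative staff to nothing; a rule put all of them on the intervention side. Any way in which they differ from station firefighters is then mixed with the effect of the programme, and larger enrolment does not dilute it.

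A difference is plausible on the protocol's own account. Section 2.1 attributes obesity and risk clustering in the fire service partly to shift work, irregular meal times and fire-service eating traditions. Much of the programme in section 4.6 is delivered through the house: sessions in its kitchen, a station champion, mailers and starter foods. People attached to no house may differ in baseline risk, in exposure to the programme and in how their outcomes change over a year.

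What is at stake is the randomised status of the main Phase 1 result. The same people could also enter later contrasts of Group 1 with Group 2: the persistence hypothesis in section 1 and the between-group biomarker changes in section 5.2. Section 6.1 stops biomarker recruitment at 30 per group, so a few administrative participants could matter there.

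**Working it through.** **Inputs from the protocol (5.1, 5.2).** Two-sided alpha 0.05; body-fat SD 6.6; planned difference 1.7 points; 250 per arm (worst case) or 500 per arm.

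**Assumed, because the protocol gives no figure.** Administrative share of Group 1, f = 5, 10 or 20%. Mean difference between administrative and station staff, d = 0.1, 0.25 or 0.5 SD.

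**Step 1. Reproduce the plan's power.** SE = 6.6 × √(2/n).
- n = 250: SE = 0.590; 1.7/0.590 = 2.880; power = Φ(2.880 − 1.960) = 82.1% (stated 82%).
- n = 500: SE = 0.417; power = 98.3% (stated 98%).

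The plan's formula is the ordinary individual-level one, with no allowance for clustering. It is kept below.

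**Step 2. Bias in an unadjusted comparison.** b = f × d × 6.6. With no true effect, the two-sided false-positive rate is Φ(−1.96 + b/SE) + Φ(−1.96 − b/SE).

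| d | f | b (points) | b as % of 1.7 | Rate, 250 per arm | Rate, 500 per arm |
|---|---|---|---|---|---|
| 0.1 SD | 5% | 0.03 | 2% | 5.0% | 5.1% |
| 0.1 SD | 10% | 0.07 | 4% | 5.1% | 5.3% |
| 0.1 SD | 20% | 0.13 | 8% | 5.6% | 6.2% |
| 0.25 SD | 5% | 0.08 | 5% | 5.2% | 5.4% |
| 0.25 SD | 10% | 0.17 | 10% | 5.9% | 6.8% |
| 0.25 SD | 20% | 0.33 | 19% | 8.65% | 12.4% |
| 0.5 SD | 5% | 0.17 | 10% | 5.9% | 6.8% |
| 0.5 SD | 10% | 0.33 | 19% | 8.65% | 12.4% |
| 0.5 SD | 20% | 0.66 | 39% | 20.1% | 35.3% |

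For a given share and difference, the rate is higher at 500 per arm than at 250, because b stays fixed while the SE falls.

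**Step 3. What changes under the planned models.** Adjustment for baseline removes much of a stable difference in level, so d must then be read as a difference in 12-month change. For the 0.66-point shift to survive, administrative staff would have to drift 0.5 × 6.6 = 3.3 body-fat points away from station staff in a year, nearly twice the planned treatment effect (3.3/1.7 = 1.9). A drift of 0.1 SD is 0.66 points and gives the first three rows on this formula.

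**Step 4. Power if they are left out.** SE = 6.6 × √(1/[250(1 − f)] + 1/250).

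| f | Group 1 v Group 2 | SE | Power, 1.7 points |
|---|---|---|---|
| 0 | 250 v 250 | 0.590 | 82.1% |
| 5% | 237.5 v 250 | 0.598 | 81.1% |
| 10% | 225 v 250 | 0.607 | 80.0% |
| 20% | 200 v 250 | 0.626 | 77.5% |

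At 500 per arm, the 20% case still has 97.0% power, against 98.3%.

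**The case against.** **Section 5.1 may already leave them out.** A person with no house cannot be classified by the randomisation of a house, and section 4.4 admits administrative staff only under a separate criterion. Analysis sets are also often left to a statistical analysis plan. This reading is possible. But Group 1 is defined to include these people in three places and no section removes them, so the reading shows that the sections conflict; it does not resolve the conflict. Who belongs to Group 1 is something this protocol states itself.

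**The large error rates rest on assumptions.** This stands. A reader might take from the table that the trial's false-positive rate is 20% or 35%. The documents do not support that: the share and the 0.5 SD difference are both assumed, and the test is unadjusted, whereas section 5.1 plans covariate-adjusted repeated-measures models for the key outcomes.

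**The direction is unknown.** This also stands. A reader might infer a bias in favour of the diet. If administrative staff had higher body fat, Group 1 would look worse. In the 0.5 SD, 20%, 250-per-arm case, 20.0 of the 20.1 percentage points would then be false findings of harm and 0.1 would be false findings of benefit. The opposite is equally possible.

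**Two further inferences go too far.** The protocol says only that administrative staff are not assigned to a specific house. It does not say that they never eat or work shifts in one. Nor must a clustered model drop them, since they can be entered as clusters of one; that deals with the correlation structure but not with the missing randomisation.

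**The biomarker study does not need them removed altogether.** Correct for the correlations and regressions of questionnaire items with biomarkers, which do not rely on randomisation.

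**Conclusion.** The point holds as a conflict between sections with a design consequence. Sections 1, 4.4 and 6.1 put a non-randomised subgroup in Group 1 with no counterpart in Group 2. Section 5.1 labels the comparison of those groups intention to treat by house randomisation, a rule that cannot be applied to people without a house. If Group 1 is analysed as defined, the contrast is partly non-randomised, whatever the size of the resulting bias.

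That size and its direction cannot be derived from the protocol. The range shown runs from negligible (0.1 SD: at most 5.6% at 250 per arm and 6.2% at 500) to serious (0.5 SD with a 20% share: 20.1% and 35.3%). All of it is conditional on assumed shares of 5 to 20%, an unadjusted test and no clustering. With baseline adjustment only differences in 12-month change matter, and these may be small. With the number affected unknown and a remedy available at analysis, this is a matter that should be fixed; the documents do not show that the main result would be invalid.

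**What to change.** - **Section 5.1:** define the primary Phase 1 comparison as participants permanently assigned to one of the 44 randomised houses. Apply the same set to any later randomised Group 1 v Group 2 comparison, including persistence and between-group biomarker change.
- **Sections 1, 4.4 and 6.1:** keep administrative staff in the programme, but describe and flag them as a non-randomised cohort. Report them separately, with an analysis that pools them into Group 1 only as a sensitivity analysis.
- **Biomarker study:** they may stay in for the questionnaire-validation correlations.
- **Section 4.3:** count the minimum of 500 on station-assigned participants.

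The cost is wording, one indicator variable and a little power: for body fat at 250 per arm, from 82.1% to 81.1, 80.0 or 77.5% if administrative staff are 5, 10 or 20% of Group 1. Counting the minimum on station-assigned participants protects against that loss, provided the two arms stay balanced.

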## 2. Background

### 2.1 Provide the scientific background and rationale for the study

**Cardiovascular disease (CVD)** is the leading cause of on-duty death (about 45% of on-duty fatalities) and lifetime mortality (at least 30% of all deaths), as well as morbidity among US firefighters. Thus, interventions which prevent CVD are clearly the top priority for US fire service research. The effectiveness of the Mediterranean diet in preventing CVD is roughly equivalent to statin medications (e.g. Lipitor, Crestor), but without side effects; while providing added benefits on weight control, diabetes prevention and decreased cancer risk, however, there is little available experience with worksite implementation of Mediterranean diet.

**Obesity and cardio-metabolic risk clustering** are well-established CVD risk factors. Current evidence demonstrates a growing obesity problem in the fire service, with obesity to have documented adverse effects on: fitness, metabolic syndrome, CVD events, including SCD; injury risks/workers' compensation costs; job-related disability and CVD retirements.

**Existing Dietary Challenges and Opportunities:** Various factors contribute to the high prevalence of obesity and CVD risk clustering in the fire service, including: shift work-induce sleep disturbance/sleep deprivation; unreliable meal times which increase the risk of less optimal dietary choices and greater consumption of fast-/takeout-foods; and traditions around over-eating and less healthy food choices common in fire service culture. According to our recent study, the two dietary factors that differed the most between obese and non-obese firefighters were obese firefighters' higher consumption of sugary drinks and fast-food.

**Mediterranean Diet on CVD and Cancer risk reduction:** Mediterranean-style diets are similar eating habits traditionally followed in countries bordering the Mediterranean Sea. The general pattern is characterized by high consumption of olive oil, fruits, vegetables, unrefined (whole grain) breads and cereals, legumes and nuts; moderate consumption of fish and poultry; a relatively low intake of dairy products; and low-sparing consumption of red meat, processed meats and sweets.

Numerous studies have demonstrated the effectiveness of Mediterranean diets in reducing all-cause mortality, CVD morbidity and mortality and cancer mortality. The mechanisms are likely mediated through beneficial effects on CVD risk factors such as obesity, hypertension, diabetes mellitus and metabolic syndrome. Given these clear benefits, the latest US government nutritional guidelines recognize and recommend the Mediterranean Diet as one of three healthy options for Americans.

**Mediterranean Diet and Workplace Behavioral Change:** As we recently summarized in a published review of Mediterranean diet and the workplace, experience with worksite MDNIs is limited, but the evidence is quite positive. Shai et al. conducted the only randomized controlled trial at an Israeli nuclear facility. Over 300 obese participants were randomly assigned to: a low-fat, restricted-calorie diet; a Mediterranean, restricted-calorie diet;

or a low- carbohydrate diet without calorie restriction. After 2 years, the mean weight loss was 2.9 kg in the low-fat group, 4.4 kg in the Mediterranean group, and 4.7 kg in the low carbohydrate group. The participants were then followed for an additional 4 years without active intervention. After 6-years, the total weight loss was greatest and most significant for the Mediterranean group (3.1 kg), whereas the other two groups gained back most of their weight.

**Preliminary cross-sectional data among firefighters showed that** greater adherence to a Mediterranean dietary pattern as measured by the modified Mediterranean diet score (mMDS) was significantly associated with improvements in body fat, metabolic syndrome, LDL- and HDL-cholesterol, weight, and aerobic fitness. Dietary modification is more likely to be effective when the strategy is appealing to the target population and addresses perceived knowledge gaps. A national survey that our group conducted demonstrated that a majority of career firefighters (71%) do not currently follow any particular dietary plan, feeling that they receive insufficient information from the fire service on nutrition, while they are interested in learning more about nutrition and healthy eating and over 60% wanted to learn more about the Mediterranean diet. The survey rankings demonstrate that while most firefighters reject a strictly plant-based diet, they are very receptive to a Mediterranean diet and rank it the highest.

Biomarkers and diet evaluation of food or nutrient intake are directly measured and can objectively estimate the consumption of specific dietary items without self-reporting biases and inaccuracies. Thus, by randomly assessing the adherence biomarkers within both the MD and control arms subsets of firefighters participating in the cluster-randomized controlled trial (Feeding America's Bravest), we can also better determine the validity of our dietary questionnaires with respect to Mediterranean diet-desirable fats. Blood samples can be used for further metabolomics analyses that will help us develop short-term indicators for assessing the effect of nutritional changes.

**In summary**, the negative effects of obesity and CVD on the fire service are recognized, but few effective preventive programs exist, and behavior change strategies must be improved. Evidence suggests that a Mediterranean diet nutrition intervention would be effective and well-received by career firefighters.

